### Additional consent provisions for collection and use of participant data and biological specimens {26b}

Not applicable.

### Interventions

#### Explanation for the choice of comparators {6b}

Not applicable. A control/placebo group is not a part of the study design.

#### Intervention description {11a}

This trial follows Danish standard clinical care and treatment published by DACSUHS [8]. Placement of a subdural drain is the standard treatment, and the only deviation is the drainage time. Blood samples are obtained routinely at admission.

In the sub-study, extra blood will be collected and stored, and CSDH fluid and the surrounding membrane will be removed during surgery. This biological material will be collected and stored for later analyses together with fluid collected from the drain during the postoperative period. The results from the sub-study will be published separately.

#### Criteria for discontinuing or modifying allocated interventions {11b}

Discontinuing of the study after randomization can occur in the following situations:
Signs of infection around the drain tubePronounced leakage from the drain canalPatient and/or relative (in case of incapacitated patients) request to withdraw from the studyDeterioration of the condition which thereby requires repeat surgery or craniotomy during primary hospitalization

#### Strategies to improve adherence to interventions {11c}

The surgeon will state in the medical record the time at which the envelope with the randomization result must be opened (6 h after surgery for all patients). This time will also be stated on the board by the patient’s bed. If the drain is to be removed after 12 or 24 h, the exact time of drain removal is written in the medical journal and on the board after the opening of the randomization envelope at the 6 h time point. A member of the research team will continuously monitor whether this process is carried out correctly.

#### Relevant concomitant care permitted or prohibited during the trial {11d}

All patients receive a standard operation and standard postoperative care. No specific care or interventions are prohibited.

#### Provisions for post-trial care {30}

Neither provisions for ancillary and post-trial care (if any) nor compensation to those who suffer harm from trial participation (if any) are provided by the neurological departments or the DACSUHS consortium. All care and help needed after discharge is provided by the Danish Health Authorities free of charge.

Everyone who receives treatment or purchases medicine in Denmark is covered by the Patient Compensation Association and can file a claim for an injury sustained as a result of the treatment or medication. This also covers participation in clinical trials.

### Outcomes {12}

#### Primary outcome measure

The primary outcome measure is the recurrence rate of chronic subdural hematoma at 3 months postoperatively.

#### Secondary outcome measures

The following are the secondary outcome measures:
Mortality rate at 90 days.Cause of death (e.g., related to recurrence, a symptomatic complication post-surgery comorbidities).Modified Rankin Scale at 90 days (Table 1).Patient-reported health status assessed by the SF-36 questionnaire (during admission and at 90 days follow-up).Length of hospital stay (at the department of neurosurgery before discharge to home or transfer to another hospital).Complications related to the drain such as bleeding from the skin, pain, general discomfort, and infection will be monitored as long as the patients are admitted to the neurosurgical department, and therefore, the observation period can vary. Drain-related complications are not to be graded regarding severity, but as “yes or no.” Time (hours) of the onset of symptoms post-surgery will also be noted.Complications related to immobilization such as deep venous thrombosis and/or pulmonary embolism and brain infarction will be monitored as long as the patients are admitted to the neurosurgical department, and therefore, the observation period can vary. These complications will be noted as “symptomatic” or “asymptomatic.” The time (hours) of the onset of symptoms post-surgery will also be noted.Sub-analyses of patients with recurrence at 90 days: co-morbidities, medications, age, gender, and evaluation of hematoma subtypes on CT from admission (homogenous, separated, mixed, or membranous [2]).

**Table 1 Tab1:** Modified Rankin Scale (mRS)

mRS score	Description
0	No symptoms
1	No significant disability despite symptoms; able to carry out all usual duties and activities
2	Slight disability; unable to carry out all previous activities but able to look after own affairs without assistance
3	Moderate disability: requiring some help (e.g., with shopping/managing affairs) but able to walk without assistance
4	Moderately severe disability: unable to walk without assistance and unable to attend to own bodily needs without assistance
5	Severe disability; bedridden, incontinent, and requiring constant nursing care and attention
6	Dead

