## Introduction

### Background and rationale {6a}

Chronic subdural hematoma (CSDH) is one of the most common neurosurgical conditions, especially in older patients, and causes serious morbidity and mortality [1]. It consists of a collection of partly or totally liquefied old blood on the brain’s surface between the dura mater and arachnoid [2]. The exact pathogenesis of CSDH remains unclear, but head trauma is known to be an important factor. CSDH can develop following only a minor injury to the head but also in the absence of a known trauma [1]. Symptoms of CSDH depend upon the size of the hematoma and specific location and may include headache, focal neurological deficits, speech problems, gait disturbance, falls, cognitive decline, confusion, and decreased consciousness. Patients with significant symptoms are admitted to a neurosurgical department for operative treatment. Burr-hole evacuation is the standard procedure in most centers. However, recurrence of CSDH is observed in 5–20% of patients, requiring readmission and further surgery. Although it is still debated whether to use subperiosteal versus subdural drain [3], there is evidence that postoperative drainage is effective in reducing the symptomatic recurrence of CSDH [4]. The shortest possible postoperative drainage period without compromising the drainage effect is preferable, both from a medical and a health economic perspective. It has been shown to be much more advantageous to remove the drain at 48 h compared to 96 h as the rate of morbidities was significantly decreased [5]. Unpublished data from a newly terminated Danish multi-center, randomized controlled trial (DRAIN-TIME 1) of postoperative drainage time could not show 48 h drainage to be superior to 24 h regarding the recurrence rate or death at 3 months.

DRAIN-TIME 2 is a nationwide, multi-center, randomized controlled trial investigating the shortest possible subdural drainage time without significantly increasing the recurrence rate. Patients will be randomized to a postoperative drainage period of 6, 12, or 24 h. The potential impact of this study is significant as we believe that a shorter drainage period may be associated with fewer drain-related complications, fewer complications related to immobilization, and shorter hospital stays.

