#### Trial rationale

We hypothesize that a drainage period of 6 and/or 12 h is non-inferior to 24 h of drainage regarding recurrence rate, and we hypothesize that the shortest possible drainage time is associated with fewer drain-related complications, faster mobilization, and shorter hospital stays.

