The Short Form-36 Health Survey is a validated, 36-item, patient-reported measure of health-related quality of life (HRQOL) that has been used in a wide spectrum of medical conditions [19–21]. It is one of the most extensively used tools to measure health-related quality of life. It covers eight dimensions of HRQOL (physical functioning, role-physical, bodily pain, general health, vitality, social functioning, role-emotional, and mental health) and has an item on general health perception. Dimension scores can be summed together with differing weightings to generate two summary scores—a physical component score and a mental component score. Higher scores indicate higher HRQOL, and the SF-36 scores range from 0 (worst) to 100 (best) [21]. In the DRAIN-TIME 2 study, the first SF-36 is completed during the initial hospital stay with assistance from a member of the research group. The questionnaire is completed electronically in the REDCap database, via a computer or tablet (Ipad). A second SF-36 questionnaire is given to the patient at discharge and is also sent by secure electronic post (E-boks) to the patient 85 days after surgery. A member of the research group will ring the patient and assist with the completion of this questionnaire after 3 months (approx. 90 days). The responses are entered directly into the online REDCap database.

Using the electronic medical record system, we will collect several data points of interest throughout the study period: number of hours post-surgery before the patient is mobilized and length of hospital stay (i.e., at the department of neurosurgery before discharge to home or transfer to another hospital).

The following will be assessed by direct daily observation during admission to the neurosurgical department: complications related to immobilization (deep venous thrombosis and/or pulmonary embolism, brain infarction) and drain-related complications such as bleeding from the skin, pain, general discomfort, and infection.

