#### Secondary outcomes

Mortality at 3 months will be analyzed by relative risk regression as with the primary outcome. SF-36, mRS, hours until mobilization, and length of hospital stay will be analyzed by linear or ordinal regression. The occurrence of different types of complications among the three study groups will be analyzed with a log-linear Poisson regression model.

For all secondary outcome measures, we investigate the superiority of each of the two experimental arms compared to the active control arm at the final analysis.

We use two-sided tests with a significance threshold of 0.05.

The data analysis will be an intention-to-treat analysis.

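### Thrombosis, embolism, brain infarction and infection are counted only until the patient leaves neurosurgery, which could favour the short-drainage arms if they leave earlier

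*Protocol article*

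**What the plan says.** The Secondary outcome measures list names two families of complications: drain-related (skin bleeding, pain, discomfort, infection) and immobilization-related (deep venous thrombosis, pulmonary embolism, brain infarction). Both "will be monitored as long as the patients are admitted to the neurosurgical department, and therefore, the observation period can vary". The section on plans for assessment and collection of outcomes {18a} confirms this: "The following will be assessed by direct daily observation during admission to the neurosurgical department". Onset in hours after surgery is recorded for both families.

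The same list makes length of stay in the neurosurgical department, ending at discharge home or transfer, a secondary outcome. The Trial rationale hypothesises that "the shortest possible drainage time is associated with fewer drain-related complications, faster mobilization, and shorter hospital stays". The Background {6a} adds the other family: "a shorter drainage period may be associated with fewer drain-related complications, fewer complications related to immobilization, and shorter hospital stays".

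In the statistical methods {20a}, complication occurrence is "analyzed with a log-linear Poisson regression model". Each short arm is tested for superiority over 24 h, two-sided at 0.05. Recurrence, mortality, the modified Rankin Scale and SF-36, by contrast, are all assessed at 90 days.

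**The concern.** Follow-up for these complications ends when the patient leaves the department, and the trial expects treatment to bring that moment forward. Take a patient transferred on day 2 who has an embolism on day 3: the record shows no event. Had the same patient still been in the department, the event would count. If the short arms leave earlier, more of their events go unrecorded, and the superiority test can read the gap as a benefit of shorter drainage.

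Fewer complications is one of the benefits put forward for shorter drainage, so a false finding here would influence how a non-inferior recurrence result is used. The primary outcome is not affected.

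**Working it through.** **Inputs from the article.** 724 per arm at the final stage (Sample size {14}); two-sided 0.05; drainage differences from control of 24 − 6 = 18 h (0.75 day) and 24 − 12 = 12 h (0.5 day).

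**Check of the 724.** With 16.3% recurrence in both arms, a 7% margin, one-sided 0.025 and power 0.95: n = 2 × 0.163 × 0.837 × (1.960 + 1.645)² / 0.07² = 723.6, so 724. The figure reproduces. It is used below only as n.

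**Assumptions, because the article gives no values.** Control stay L of 3 days (2 and 5 days as alternatives); stay shorter by d = 0.25, 0.5 or 0.75 day, the last two being the full drainage difference passed on to stay; control complication risk p_c of 2%, 5%, 10% or 20%; the same hazard in both arms, so no true effect.

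**Constant hazard.** Recorded risk in the short arm: p_e = 1 − (1 − p_c)^((L − d)/L). Standard error of the log risk ratio: √[(1 − p_c)/(n p_c) + (1 − p_e)/(n p_e)].

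Example with p_c = 5%, L = 3, d = 0.75: p_e = 1 − 0.95^0.75 = 0.0377. The risk ratio is 0.0377/0.05 = 0.755 and its log is −0.281. The standard error is 0.248, so the test statistic is shifted by −1.13. The chance of a significant result is 0.206, of which 0.205 favours short drainage.

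For a 3-day control stay:

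| Stay shorter by | Spurious risk ratio | False-positive rate at 2%, 5%, 10%, 20% risk |
|---|---|---|
| 0.25 day | 0.92 | 0.06, 0.07, 0.08, 0.11 |
| 0.5 day | 0.84–0.85 | 0.08, 0.12, 0.18, 0.32 |
| 0.75 day | 0.75–0.77 | 0.11, 0.21, 0.36, 0.62 |

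With d = 0.75, a 5-day control stay gives ratios of 0.85–0.86 (false-positive rate 0.07–0.26). A 2-day stay gives 0.63–0.65 (0.20–0.94).

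**Front-loaded hazard.** Here the hazard decays with an assumed constant of 2 days and stays are gamma-distributed with shape 4. The expected count is proportional to 1 − (1 + L/8)^(−4):

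- L = 3: 0.720
- L = 2.5: 0.663, ratio 0.92
- L = 2.25: 0.629, ratio 0.87
- L = 2.75: 0.693, ratio 0.96

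A 4,000-run simulation at d = 0.5 and 0.75 gave ratios of 0.87–0.92 and false-positive rates of 0.05–0.12. These runs kept the same initial rate, so control events are only (2/3) × 0.720 = 0.48 of the constant-hazard number. The false-positive rates are therefore not like for like with the table; the ratios are.

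**Checks.** With equal stays the simulated false-positive rate is 0.05–0.06. With a fixed 90-day window in both arms it is 0.04–0.06 in every scenario. A log(stay) offset restores 0.04–0.05 under a constant hazard. Under the front-loaded hazard it overcorrects, with rate ratios of 1.10–1.18 and false-positive rates of 0.06–0.14.

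**The case against.** Several points on the other side stand:

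- **The bias is conditional.** It needs stays to differ by arm and risk to continue after departure. A reader might infer that the short arms will show fewer complications whatever happens. The article does not support that: it reports no stay lengths, and with equal stays nothing is distorted.
- **Not all complications are alike.** Planned drainage is at most 24 h in every arm. If skin bleeding, pain and discomfort cluster while the drain is in place, they are largely observed in all arms, and fewer of them may be the hypothesised true effect.
- **The larger figures need favourable assumptions.** At an assumed 2% risk, plausible for thrombosis or embolism, a 3-day stay shortened by 0.75 day gives a false-positive rate of only 0.11.
- **The limitation is disclosed.** The article says that observation can vary and records onset hours. Mortality, cause of death and the Rankin score to day 90 partly capture severe late events.
- **The choice of Poisson model is not a fault to press.** Plain Poisson standard errors on yes/no data are too wide, which makes a spurious significant result less likely. Offsets and robust variance are commonly left to an analysis plan.

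The reply that an analysis plan could add an offset does not dispose of the point. The window is a data-collection rule set in the protocol. No model recovers events that were never recorded, and the offset is unbiased only under a constant hazard.

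**Conclusion.** The concern holds in limited form, for deep venous thrombosis, pulmonary embolism, brain infarction and drain infection. Their counting stops at an event that the trial expects shorter drainage to hasten, and the short arms are tested for superiority on what was counted. If stay differs by arm, this could produce an apparent benefit with no true effect.

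Under the assumed 3-day control stay the spurious ratio is about 0.75 to 0.92 with a constant hazard and a 0.25 to 0.75 day difference. It is 0.87 to 0.92 with a front-loaded hazard and a 0.5 to 0.75 day difference. The direction follows from the article's own hypothesis; the size rests on assumed stays, risks and hazard shapes.

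It might also be inferred that fewer complications is the principal claimed benefit. The article lists complications beside mobilization and length of stay, and its Discussion also stresses bed turnover and health economics. This is a secondary-outcome matter that should be corrected; it does not threaten the recurrence comparison.

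**What to change.** - **Later-onset events.** Count symptomatic thrombosis, embolism, brain infarction and infection over one fixed window from surgery, identical in all arms (for example to day 90). Add these items to the record review and telephone call already planned at 90 days, and base the between-arm comparison on that window.
- **In-department counts.** Report them, including asymptomatic events, as descriptive.
- **Skin bleeding, pain and discomfort.** Use the recorded onset hours to restrict the comparison to a common early postoperative window in which nearly all patients in every arm are still under observation.

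The cost is a few extra data items per patient, for up to 2172 patients, and a wording change in the protocol. The article describes the record review for recurrence and death, and the call for capacity, the Rankin score and SF-36, so both forms need extending. Events treated elsewhere may still be captured incompletely, and a longer window admits some events unrelated to drainage, which dilutes the contrast. Neither drawback depends on arm in the way that the present window does.

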#### Exploratory (mechanistic) outcome measure (sub-study)

To explore possible mechanisms and thereby potential therapeutic targets for reducing recurrence risk, the peripheral and central (local) inflammatory responses will be assessed by collecting blood samples, CSDH fluid, and a biopsy of the surrounding membranous tissue during surgery together with CSDH fluid from the postoperative draining period. Proteomic analysis and inflammatory marker analysis of the collected material will serve as a descriptive study; the results will be compared between recurrent and non-recurrent patients to assess whether the differences in inflammatory mechanisms play a role in the development of recurrent CSDH. The following activities will be conducted:
Assess the peripheral (blood) inflammatory response in CSDH patientsAssess the composition of proteomics and inflammatory and angiogenetic markers in the CSDH fluid from surgery and in the fluid obtained during the draining periodTo do immunohistochemical analyses of inflammatory markers on membranous tissue removed during surgeryCompare fluid composition with hematoma subtypeCompare fluid composition between recurrent and non-recurrent patients.

The results from this exploratory sub-study will be presented in a separate paper.

#### Participant timeline {13}

As part of the routine standard care at hospital admission, all patients will have a medical history taken and a clinical examination. Table 2 shows a full schedule of trial assessments as per the SPIRIT guidelines.

**Table 2 Tab2:** Schedule of the trial enrollment, interventions, and assessments

	Enrolment	Surgery	Post-surgery		
Time point	*Ad*	*IO*	*D1*	*D2*	*3 mon*
**Enrollment**					
**Eligibility screen**	X				
**Informed consent**	X				
***Randomization***	X				
**Interventions**					
***Placement of a subdural drain (6, 12, or 24 h)***		X			
**Assessments**					
***Routine labs***	X		X		
***GCS***	X		X		
***mRS***	X		X		X
***Clinical examination***	X				
***SF-36***	X		X^#^		X
***Economic data***					X
***CSDH fluid****		X			
***CSDH membrane****		X			
***Blood****	X				

Schedule of assessments

*Ad* admission, *IO* intraoperative, *D* day, *mon* months, *GCS* Glasgow Coma Scale, *mRS* Modified Rankin Scale, *SF-36* Short Form (36) Health Survey

^*^Only collected in patients recruited to sub-study at Odense University Hospital and Rigshospitalet

^#^If not done the day of admission

#### Sample size {14}

Calculations were based on the primary outcome measure recurrence.

##### Sample size calculations

The MAMS design required the choice of a number of stages together with the choice of stage-specific decreasing significance levels together with stage-specific power levels, which result in an overall power and a familywise error rate. To inform this decision, we calculated several different designs considering two up to five stages. Stage-specific design parameters were in a try-out manner picked such that the overall power and FWER were approximately equal to 0.8 and 0.028, respectively. Especially, stage-specific significance levels for the initial stage of 0.5, 0.3, and 0.2 were considered. The final design choice was obtained from balancing the resulting expected sample sizes (for different numbers of non-inferior treatment arms) with a greater weight on the sample size in absence of non-inferior treatment arms. This resulted in a final design with five stages and decreasing stage-specific significance levels of alpha = 0.5, 0.3, 0.2, 0.1, and 0.025 together with stage-specific power levels of 0.9 for the first three stages and 0.95 for the last two stages. Stage parameters were chosen such that the overall power for the final comparison of each experimental arm (6 h or 12 h drainage) to control (24 h drainage) is approximately equal to 0.8. The familywise error rate corresponding to the design is approximately 0.028.

Assuming a recurrence rate of 16.3% on the basis of previous DACSUHS studies in all treatment arms (both experimental and control), equal allocation to all treatment arms, and a non-inferiority margin of 7%, we obtained the following cumulative sample sizes.

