### Trial design {8}

The DRAIN-TIME 2 study is a Danish multi-center, national randomized controlled non-inferiority trial with three parallel arms. The arms correspond to 6, 12, and 24 h of drainage, where the former two arms are experimental and the 24 h group is the common control arm. Online randomization with a 1:1:1 allocation will be performed.

The trial uses a multi-arm, multi-stage (MAMS) design, which enables adaptive reductions of the number of experimental arms considered during the trial, with the aim to lower the required sample size on average. The applied design is described in Bratton et al. [6]. Our trial is organized into five stages. After each stage, non-inferiority of both arms is tested during an interim analysis at stage-specific significance levels. Significant arms continue to the next stage, whereas non-significant arms can be dropped (non-binding).

The final non-inferiority test decision is taken after the final stage (or as soon as both experimental arms are stopped) and uses all available data. Interim and final analyses rely on the same primary outcome and the same non-inferiority margin.

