**Table Tabb:** 

	Stage 1	Stage 2	Stage 3	Stage 4	Stage 5
Cumulative sample size per treatment arm reaching the respective stage	91	182	344	477	724
New samples per continued treatment arm and per stage	91	91	162	133	247
Overall cumulative sample size if no arm is dropped in any stage	273	546	1032	1431	2172

After each stage, an interim analysis will be done where non-inferiority of both arms is tested at the chosen stage-specific significance levels. Significant arms continue to the next stage, whereas non-significant arms can be dropped (non-binding). Together with the chosen stage-specific significance levels, the overall pairwise type 1 error rate (for the comparison of one experimental arm to control) equals 0.025 if stopping guidelines (i.e., for dropping of arms before the final stage) are ignored. If stopping guidelines are followed, 0.025 is an upper bound for the overall pairwise type 1 error rate.

The expected sample size for the design if all arms have an identical recurrence rate of 16.3% (implying non-inferiority of both experimental arms) and stopping guidelines are followed is 1928. If both experimental arms are inferior (with recurrence rates exceeding 16.3% by at least 7%, i.e., the non-inferiority margin) and stopping guidelines are respected, the expected sample size is 690.

Sample size calculations were done in STATA17.0 using nstagebin [6, 12]. The corresponding software output is shown in supplementary material A. Reanalysis of the meta-analysis was done in R [13] together with the package miceadds [14].

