## Statistical methods

### Statistical methods for primary and secondary outcomes {20a}

#### Primary outcome

Recurrence will be treated as a binary outcome (instead of a time-to-event outcome) due to the time to recurrence being of minor clinical interest compared to the occurrence of the event itself which is of major clinical relevance. As an effect measure, we consider relative risks due to their natural interpretability.

We will use relative risk regression with treatment assignment (6 h vs. 12 h vs. 24 h drainage time) as a categorical covariate and take the different trial centers into account. Adjusted risk ratios with 95% confidence intervals for recurrence rate will be reported. We investigate a non-inferiority hypothesis with a non-inferiority margin of 7% (see the “Sample size {14}” section). We will make two comparisons—one for each experimental arm (6 and 12 h) versus the common control arm (24 h) using likelihood ratio tests. We will use a one-sided test together with stage-specific significance thresholds equaling 0.5, 0.3, 0.2, 0.1, and 0.025 for each of the five stages.

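### The familywise error rate of about 0.028 is given without its condition: it holds only if every failing arm is dropped, and under the non-binding rule it can reach about 0.046

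*Protocol article*

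**What the plan says.** All references are to the protocol article.

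- *Sample size calculations* fixes "decreasing stage-specific significance levels of alpha = 0.5, 0.3, 0.2, 0.1, and 0.025". It says that design parameters were tried until overall power and familywise error were near 0.8 and 0.028, and concludes: "The familywise error rate corresponding to the design is approximately 0.028". No condition is given.
- *Trial design {8}* says of the interim looks: "whereas non-significant arms can be dropped (non-binding"). The text below the sample size table repeats this: "Significant arms continue to the next stage, whereas non-significant arms can be dropped (non-binding"). *Interim analyses {21b}* and the section on the data monitoring committee {21a} also describe dropping as something that can be chosen.
- The text below the table then treats the pairwise error under two cases. It says that "the overall pairwise type 1 error rate (for the comparison of one experimental arm to control) equals 0.025 if stopping guidelines" are ignored, and that 0.025 is an upper bound if they are followed. The expected sample sizes of 1928 and 690 are labelled as holding when the guidelines are followed. The familywise rate has no such label.
- *Primary outcome*, under the statistical methods: "We will use a one-sided test together with stage-specific significance thresholds equaling 0.5, 0.3, 0.2, 0.1, and 0.025 for each of the five stages".

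**The concern.** Two error rates appear close together, and a reader will take them to describe the same rule. The pairwise 0.025 is explicitly the value with the stopping guidelines ignored, which is the usual basis for a non-binding rule. A familywise rate of 0.028 does not fit beside it. With two comparisons at 0.025 each, the chance of at least one false claim is 0.05 minus the chance that both are false. To reach 0.028, both would have to fail together with probability 0.05 − 0.028 = 0.022, so one false claim would bring the other with it 0.022/0.025 = 88% of the time. A shared control under 1:1:1 allocation does not produce dependence of that strength.

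The figure matters because the trial may claim non-inferiority for 6 h, 12 h or both, so the familywise rate describes its main claim. It was also one of the two targets used to choose the design. Keeping a failing arm is expressly allowed. That decision rests with the steering committee, advised by a biostatistician, and no data monitoring committee is set up.

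**Working it through.** **Inputs.** One-sided stage levels 0.5, 0.3, 0.2, 0.1 and 0.025 (*Sample size calculations*; *Primary outcome*). Cumulative patients per arm 91, 182, 344, 477 and 724, as printed in the sample size table. Recurrence 16.3%, margin 7 percentage points, 1:1:1 allocation, two experimental arms and one common control.

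**Model.** The stage-wise z statistics are taken as multivariate normal. Within a comparison, the correlation between stages i < j is √(n_i/n_j). Between the two comparisons it is

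ρ = var(control) / [var(control) + var(experimental)].

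- Equal variances: ρ = 0.5.
- At the non-inferiority boundary (16.3% control, 23.3% experimental): 0.163 × 0.837 = 0.1364 and 0.233 × 0.767 = 0.1787, so ρ = 0.1364/(0.1364 + 0.1787) = 0.433.

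**Step 1: reproduce the plan, with every failing arm dropped.** An arm yields a false claim only if it passes all five stages. The pairwise rate was checked by numerical integration; the other values come from 8 million simulated trials per scenario.

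| Quantity | Recomputed | Stated |
|---|---|---|
| Pairwise error | 0.0148 | at most 0.025 |
| Familywise error, ρ = 0.5 | 0.0275 | about 0.028 |
| Familywise error, ρ = 0.433 | 0.0279 | about 0.028 |
| Pairwise power, equal rates | 0.802 | about 0.8 |
| Expected total N, both arms inferior (ρ = 0.5) | 690.6 | 690 |
| Expected total N, equal rates (ρ = 0.5) | 1929.6 | 1928 |

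The model matches the familywise rate, the power and both expected sample sizes. The printed 0.028 is therefore the value with the guidelines always followed.

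**Step 2: the same design with the guidelines ignored.** Only the final test at 0.025 counts, so the stage sizes no longer matter:

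FWER = 1 − Φ₂(1.960, 1.960; ρ) = 0.025 + 0.025 − P(both).

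- ρ = 0.5: FWER = 0.0454, so P(both) = 0.05 − 0.0454 = 0.0046.
- ρ = 0.433: FWER = 0.0463, so P(both) = 0.05 − 0.0463 = 0.0037.
- Check, independent comparisons: 1 − 0.975² = 0.0494.

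**Step 3: size.** 0.0454/0.028 = 1.62 and 0.0463/0.028 = 1.65.

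**Side by side**

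| | Guidelines always followed | Guidelines ignored |
|---|---|---|
| Pairwise error | about 0.015 | 0.025 |
| Familywise error | about 0.028 | 0.045 to 0.046 |

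The protocol prints the pairwise value from the right-hand column, with its condition, and the familywise value from the left-hand column, without one.

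**The case against.** The best defence is that 0.028 is reported as a property of the design and not promised as a limit. The protocol sets no familywise ceiling. Its pairwise statement is correct in both cases, and the thresholds and sample sizes are the same whichever familywise figure is printed. Dropping is also the planned response to failure, and the biostatistician advises from the predefined guidelines, so a course in which every failing arm is kept to the end is an extreme. The software output in supplementary material A, which is not at hand, may state the condition.

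Most of this stands, and it rules out three stronger readings that a reader might infer.

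- *The trial's familywise rate is 0.045.* The documents do not support this. The value is reached only if failing arms are always kept, and partial adherence gives something lower.
- *The trial breaches its declared error level.* It declares none for the familywise rate.
- *The final level must be lowered, or the rule made binding.* Holding 0.028 with the guidelines ignored would need a final level of about 0.015 per comparison, but nothing in the protocol requires 0.028 to be held in that case, and recruitment is already under way.

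The defence does not remove the point itself. The article prints 0.028 without a condition beside a rule it calls non-binding, and it gives that condition for the pairwise error and the expected sample sizes. A supplement that states the condition would not correct the unqualified sentence in the text.

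**Conclusion.** The point holds as a misstated operating characteristic. The familywise rate of about 0.028 is right only if every arm failing a stage is dropped. Under the non-binding rule that the protocol adopts, the maximum is about 0.045 to 0.046, and actual conduct would fall between about 0.028 and 0.046 depending on how often failing arms are kept.

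This rests on the normal approximation, on the risk-difference scale used for sizing, on the stage sizes as printed, and on a correlation between comparisons of 0.43 to 0.5. The close match to the stated power and expected sample sizes supports the model. The guidelines-ignored figure depends only on the final level and that correlation. The validity of each pairwise test at 0.025 is not in question.

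**What to change.** In *Sample size calculations* and in the text below the sample size table, replace the single figure with both cases, for example: *familywise error rate about 0.028 if every arm failing a stage is dropped; up to about 0.046 if the non-binding stopping guidelines are ignored.* The upper figure should be 0.046 and not 0.045, because the trial's own boundary rates (16.3% and 23.3%) give 0.0463.

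The cost is wording and a less favourable published figure. Sample sizes, stage levels, the final test at 0.025 and the non-binding status of the rule all stay as they are.
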